### Efficacy

The primary endpoint is the mean change in VAS score between the OJS group and the placebo group from baseline to V5; the secondary endpoints are the mean changes from baseline at V5 in BT, WHOQOL-BREF, and CST. Both assessments will be analyzed using chi-square or Fisher’s exact tests for categorical data and Student’s *t* tests or Mann-Whitney *U* tests for continuous data. Additionally, the repeated measures analysis of variance (ANOVA) will be performed to assess the presence of any significant differences in the mean VAS, BT, and WHOQOL-BREF scores between groups at different time points (each visit after baseline assessment).

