**Methods:**

This study is a multicenter, double-blinded, randomized, placebo-controlled, two-arm, parallel-group pilot clinical trial. A total of 60 participants will be enrolled and randomly assigned to the *Ojeok-san* treatment group or the placebo control group, in a 1:1 ratio using an Internet-based randomization system. Each group will be administered *Ojeok-san* or placebo three times per day for 8 weeks. The primary outcome will be the mean change in the Visual Analog Scale scores of cold hypersensitivity in the hands from baseline to week 8. Secondary outcomes will include the mean changes in the skin temperature of the extremities, recovery rate of the skin temperature of hands after cold stress test, and the score of Korean version of the WHO Quality of Life Scale abbreviated version.

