## Methods

### Objective

We will evaluate the feasibility of a full randomized clinical trial (RCT) of OJS on Korean female patients with CHHF to evaluate CHHF symptom reduction after 8 weeks of OJS medication as compared with the placebo group.

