**Fig. 1 Fig1:**
[figure not shown]
Flow chart of study procedure

A total of 60 participants, who voluntarily confirm their willingness to participate in this trial, will be recruited. Written informed consent will be obtained after giving sufficient explanation and period of time for thoughtful decision. Once the participant agrees to participate in this trial, they will be asked to undergo several medical checkups for identifying ineligible participants. After 1 week of run-in period, qualified eligible participants will be randomly assigned to the OJS or the placebo group. They will be administered the investigational products (IP) for 8 weeks and one follow-up visit will be scheduled at 4 weeks after discontinuation of medication (Table 1). The participants will be asked to return any unused investigational drugs at every visit to monitor adherence in order to calculate compliance. During the trial, the participants will be prohibited from receiving other weight-loss treatment.

**Table 1 Tab1:** The detailed trial schedule

		Study period				
		Screening	Treatment period			Follow-up period
Visit		visit 1 (D − 7~ − 2)	visit 2 (D 1)	visit 3 (D 28)	visit 4 (D 56)	FU1 (D 84)
Informed consent		●				
Eligibility assessment		●				
Random allocation			●			
Socio-demographic investigation^a^		●				
Medical and drug history^b^		●				
IP distribution	OJS		●	●		
	Placebo		●	●		
Assessment						
General physical examination		●	●	●	●	●
Severity of CHHF (VAS)		●	●	●	●	●
Skin temperature measurement^c^		●	●	●	●	●
Quality of life (WHOQOL-BREF)			●	●	●	●
Cold stress test			●		●	
Vital signs		●	●	●	●	●
*Anthropometric variables*		●	●	●	●	
Chest x-ray and EKG		●				
Clinical pathological laboratory test		●			●	
Medical and drug history check-up			●	●	●	●
Adverse event check-up				●	●	●
Compliance check-up				●	●	
Blind assessment					●	

^a^Sex, date of birth, age, level of education, occupation, marital status, diet, exercise, smoking, drinking, sleeping condition, motivation of participation, etc.

^b^Including medical and drug history of CHHF

^c^Skin temperature of palm (PC9) and anterior upper arm (LU4) will be measured at the screening visit; skin temperature of thigh (ST32) and instep of foot (LR3) will also be collected additionally at visit 2

Abbreviations: *CHHF* cold hypersensitivity in the hands and feet, *EKG* electrocardiogram, *IP* investigational products, *OJS ojeok-san*, *VAS* Visual Analog Scale, *WHOQOL-BREF* WHO Quality of Life abbreviated version

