##### Cold stress test

The cold stress test (CST) is generally used to assess the severity of cold sensitivity in patients with vascular disorders [18]. For performing the procedure, the participants will rest for 20 min in the examination room (24 ± 1 °C) and then immerse both hands into a container of iced water (20 °C) for 30 s. The BTs of both palms (PC8) are assessed by using an infrared thermometer (Testo 835-T1, Lenzkirch, Germany), pre and post immersion and 6 min post immersion. The CST will be performed at visits 2 and 5. The recovery rate (RR) equation of the CST is as follows:$$ RR=\left({T}_6-{T}_0\right)/\left({T}_{\mathrm{base}}-{T}_0\right)\times 100\%, $$

where: *T*_base_: the skin temperature of PC8 at pre immersion

*T*_0_: the skin temperature of PC8 measured at post immersion

*T*_6_: the skin temperature of PC8 measured at 6 min post immersion

The higher RR represents faster recovery to normal temperature. The mean change of RR from baseline will be calculated to evaluate the efficacy of OJS.

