##### Korean version of the WHO Quality of Life-BREF

The mean changes of the WHO Quality of Life abbreviated version (WHOQOL-BREF) score from baseline will be assessed the quality of life of patients with CHHF symptoms. The WHOQOL-BREF is an effective, cross-culturally comparable, quality of life questionnaire. It consists of 26 items with five domains: general quality of life (2), physical health (7), psychological health (6), social relationships (3), and environmental health (8). To estimate quality of life scores in the Korean population, the Korean version of WHOQOL-BREF by Min et al. [19], will be used and measured at visits 2 and 4. Raw scores in each domain will be converted into a 0–100 transformed score where a higher score indicates better quality of life.

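### The Efficacy section sets the primary and secondary endpoints at a visit V5 that the schedule does not contain; week 8 (visit 4) is the better-supported meaning and should be written in

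*Protocol article*

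**What the plan says.** The time point for efficacy is stated or implied in several places in the protocol article:

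- **Efficacy section, primary:** "The primary endpoint is the mean change in VAS score between the OJS group and the placebo group from baseline to V5".
- **Efficacy section, secondary:** "the secondary endpoints are the mean changes from baseline at V5 in BT, WHOQOL-BREF, and CST".
- **Abstract, Methods:** the primary outcome is the VAS change for "cold hypersensitivity in the hands from baseline to week 8".
- **Objective:** the trial is meant "to evaluate CHHF symptom reduction after 8 weeks of OJS medication as compared with the placebo group".
- **Table 1:** visit 1 (screening), visit 2 (D1), visit 3 (D28), visit 4 (D56) and FU1 (D84). The text beside it says that "one follow-up visit will be scheduled at 4 weeks after discontinuation of medication".
- **Cold stress test section:** "The CST will be performed at visits 2 and 5". Table 1 marks the CST at visits 2 and 4 only.
- **WHOQOL-BREF section:** the questionnaire "will be used and measured at visits 2 and 4". Table 1 marks it at visits 2, 3, 4 and FU1.

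The section that defines the VAS as primary outcome gives no end time point. It says that the VAS is recorded at all visits.

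**The concern.** The Efficacy section is the part of the article that tells the analyst which comparison to make, and it names a visit that the schedule does not have. A reader who counts the columns of Table 1 arrives at FU1 as the fifth contact, when participants have been off the study drug for 4 weeks. A comparison there asks whether an effect persists after stopping. A comparison at week 8 asks whether there is an effect at the end of treatment, which is what the abstract and the objective describe.

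The VAS, on which the primary endpoint rests, is collected at both times, so missing data would not expose a wrong reading. The CST is different. If V5 meant FU1, there would be no scheduled CST from which to compute the endpoint. Staff who followed the CST text rather than Table 1 could also carry out the second test at the wrong visit, and analysis could not repair that.

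**Working it through.** No sample size, power or significance figure depends on the label, and the article says that no sample size was calculated. The check is therefore a comparison of visit labels, days and scheduled measurements.

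**Days to weeks (Table 1)**
- Visit 4: 56 / 7 = 8 weeks, the end of treatment.
- FU1: 84 / 7 = 12 weeks, which is (84 − 56) / 7 = 4 weeks after the end of treatment.
- Whole study: 7 screening days + 84 days = 91 days, and 91 / 7 = 13 weeks. This matches the duration given under Trial design and setting, so no further visit after FU1 has dropped out of the table.

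**What is scheduled at each candidate time (Table 1)**

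| Endpoint given as V5 | Visit 4, D56 | FU1, D84 |
|---|---|---|
| VAS | yes | yes |
| Skin temperature | yes | yes |
| WHOQOL-BREF | yes | yes |
| CST | yes | no |

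The Efficacy section applies one label to all four endpoints. Of the two candidates, only D56 has all four measured.

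**Where the label can be tested**
The CST is the one outcome whose text and table both list its visits. The text has 2 and 5, and Table 1 has 2 and 4. There, visit 5 in the text corresponds to D56 in the table. The baseline visit carries the number 2 in both, so the text has not simply moved every visit number up by one.

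**Agreement with the rest of the article**
- Reading V5 as visit 4 agrees with the abstract (week 8), with the objective (8 weeks of medication) and with the CST row of Table 1. Only the label in the Efficacy and CST sections is then wrong.
- Reading V5 as FU1 contradicts the abstract and leaves the CST endpoint unmeasured.

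**WHOQOL-BREF**
Text and Table 1 agree on visit 2 and visit 4, the two values that a week-8 change needs. They differ on visit 3 and FU1. The difference matters for the additional repeated-measures ANOVA, which is to cover VAS, skin temperature and WHOQOL-BREF at every post-baseline visit. Under the text, WHOQOL-BREF has one post-baseline time (visit 4). Under Table 1 it has three (visits 3, 4 and FU1).

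**The case against.** The strongest reply is that the article largely answers the question itself. The abstract states week 8 outright, and the article appeared while enrolment was still open. Nowhere is D84 or week 12 named as an efficacy endpoint, and Table 1 calls that contact FU1 rather than giving it a visit number. The one checkable use of visit 5 lines up with D56. An independent statistician is to analyse the data blind. On this view V5 is a slip that no careful analyst would follow to FU1.

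Most of that stands, and it limits the point. A reader might infer that the primary estimand is undetermined, or that it has moved off treatment. The documents do not support this, because week 8 is clearly the better-supported meaning. A reader might also want to attach a loss of power or an inflated type I error from a choice between two time points. Any such figure would need an effect size, a degree of persistence after stopping and a correlation between visits, and the protocol gives none of these. Nor does WHOQOL-BREF lack a consistent measurement time for the week-8 comparison, since baseline and D56 agree in both places.

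The reply does not make the Efficacy section correct. The label appears twice there and again in the CST section, so it is not a single misprint. The objective supports week 8 but names neither the VAS nor a primary endpoint, so the abstract alone fixes the time for the primary outcome. An abstract should not have to overrule the analysis text.

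**Conclusion.** The point holds as an internal contradiction. One primary and three secondary endpoints are set at a visit that does not exist, and the ordinal reading of that visit falls 4 weeks (28 days) after the intended end-of-treatment comparison. V5 is most likely a mislabel of visit 4. That conclusion rests on the abstract, the objective and the CST row of Table 1, and on no outside assumption.

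The size is not numerical: no power, sample size or type I error figure in the protocol changes. Correction is still needed because the primary time point is involved, VAS data will exist at both days, and the article reports 50 of the planned 60 participants already recruited. The WHOQOL-BREF discrepancy is a smaller, separate matter confined to the repeated-measures analysis.

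**What to change.** Before database lock:

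1. In the Efficacy section, replace V5 by visit 4 (D56, week 8) for the primary endpoint and for skin temperature, WHOQOL-BREF and CST.
2. In the Cold stress test section, change the visits to 2 and 4, as in Table 1.
3. Reconcile the WHOQOL-BREF section (visits 2 and 4) with Table 1 (visits 2, 3, 4 and FU1), checking the case report form for the visits actually used, so that the repeated-measures ANOVA refers to data that exist.

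No new FU1 endpoints are required, because the repeated-measures analysis already takes in the later visits. The cost is a wording correction in the protocol, and in the analysis plan if it carries the same label. No new visits, measurements or participants are needed.

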
### Randomization

An independent professional statistician from the contract research organization (CRO), the Institute of Safety, Efficacy, and Effectiveness Evaluation for Korean Medicine (ISEE), will be created with a block size of 2 or 4 and hospital stratification by using SAS (version 6.1.; SAS Institute Inc., Cary, NC, USA). The ISEE also develops and controls the web-based randomization system with an allocation ratio of 1:1. Randomization number assignment via the web-based system will be performed at visit 2 by site the clinical research coordinator (CRC) or research assistants. The randomization sequence table will be kept in the opaque sealed envelope by the CRO and should be opened according to Standard Operating Procedures (SOPs).

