### Recruitment

A total of 60 participants who meet the eligible criteria will be competitively recruited from three sites of university-affiliated Korean medicine teaching hospitals. Patient recruitment will be advertised by using posters and institution website bulletin boards in trial hospitals or local community newspaper advertisements.

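### The unadjusted t or Mann-Whitney test on VAS change is valid but generally gives away precision, because it fixes the baseline slope at 1 and leaves out the hospital strata

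*Protocol article*

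**What the plan says.** - **Endpoint (Efficacy):** "The primary endpoint is the mean change in VAS score between the OJS group and the placebo group from baseline to V5". For the others, "the secondary endpoints are the mean changes from baseline at V5 in BT, WHOQOL-BREF, and CST".
- **Test (Efficacy):** for continuous outcomes, Student's t "tests or Mann-Whitney *U* tests for continuous data". Neither a covariate nor a stratum is named.
- **Further analysis (Efficacy):** "Additionally, the repeated measures analysis of variance (ANOVA) will be performed" for VAS, BT and WHOQOL-BREF. It also names no baseline covariate and no hospital term.
- **Design (Randomization, Recruitment):** the allocation sequence "will be created with a block size of 2 or 4 and hospital stratification", "with an allocation ratio of 1:1". Patients are "competitively recruited from three sites of university-affiliated Korean medicine teaching hospitals", so hospital sizes are not fixed in advance.
- **Data at hand (Table 1):** VAS, skin temperature, WHOQOL-BREF and the cold stress test are all recorded at visit 2, before treatment.
- **Entry limit (Table 2):** VAS of 4 or higher.
- **Sample size:** 60 patients, 30 per group, expressly without a calculation.

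**The concern.** A change score uses the baseline, but forces its slope to be 1. When the true slope of week-8 VAS on baseline VAS is below 1, this subtracts too much of the baseline, and the surplus appears as noise in the treatment comparison. ANCOVA estimates the slope instead.

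Hospital is a separate matter. Stratified randomization balances the arms within hospital. If hospitals differ in how much VAS changes, the treatment estimate already benefits from that balance, but a two-sample test still counts the between-hospital variation in its standard error.

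At stake is the width of the interval around the effect estimate. The article says this pilot is to inform a large trial, so its estimate and spread will probably be used for planning. Variance that could have been removed at no cost makes both less informative.

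**Working it through.** The article gives no power, effect size or SD, so there is no stated figure to reproduce. Taken from the article: N = 60, 30 per group, three hospitals, blocks of 2 or 4, and a 0.05 level (two-sided assumed). Assumed: the baseline/week-8 correlation rho, the SD ratio k = baseline SD / week-8 SD, and the spread between hospitals.

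**1. Precision with equal SDs (k = 1).** With common SD s:
- Var(change) = 2(1 − rho)s²
- Var(ANCOVA) = (1 − rho²)s²
- Ratio = (1 + rho)/2

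| rho | Ratio | Unadjusted N matching 60 adjusted |
|---|---|---|
| 0.3 | 0.65 | 60/0.65 = 92 |
| 0.5 | 0.75 | 60/0.75 = 80 |
| 0.7 | 0.85 | 60/0.85 = 71 |

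As an illustration, take rho = 0.5 and a difference of 0.5 SD. The SD is 1.000 for change and √0.75 = 0.866 for ANCOVA, and the standard-error multiplier is √(2/30) = 0.258. Power is then 49% against 61%.

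**2. Precision with unequal SDs.** In general the ratio is (1 − rho²)/(1 + k² − 2·rho·k). It equals 1, meaning no gain, when k = rho, that is, when the true slope is 1.
- rho 0.5, k 0.8: 0.75/0.84 = 0.89
- rho 0.5, k 0.6: 0.75/0.76 = 0.99
- rho 0.5, k 0.5: 0.75/0.75 = 1.00
- rho 0.7, k 0.8: 0.51/0.52 = 0.98

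The entry limit of VAS 4 or higher truncates the baseline range but not the week-8 range, so k below 1 is plausible. The article gives no SD to settle it.

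**3. Hospital strata: error rate.** Simulation with N = 60 (20 per hospital), blocks of 2 or 4, rho = 0.5, equal SDs, and hospital effects acting on VAS change and scaled to an exact share of its variance. There were 4,000 null runs per setting (Monte Carlo SE about 0.34 percentage points).

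| Hospital share of change variance | t test | Mann-Whitney | ANCOVA + hospital |
|---|---|---|---|
| 0 | 4.8% | 4.7% | 4.8% |
| 0.05 | 4.5% | 4.1% | 4.6% |
| 0.1 | 3.6% | 3.5% | 4.4% |
| 0.2 | 3.1% | 2.8% | 5.4% |
| 0.3 | 1.5% | 1.6% | 5.0% |

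Hospital sizes of 30/20/10 gave similar results. With no hospital effect, omitting the baseline leaves the error rate at nominal (4.3% to 5.3% for the two unadjusted tests across all such settings). The conservatism therefore comes from omitting hospital alone.

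**4. Hospital strata: power.** Same set-up, with a true difference of 0.65 SD and 2,000 runs. For t / Mann-Whitney / ANCOVA with hospital, power was 70 / 68 / 81% at share 0, 67 / 64 / 83% at 0.1, and 56 / 52 / 82% at 0.3.

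**5. Sensitivity to how hospitals differ.** With SD 1.5 and rho 0.5, drawing the three hospital effects at random rather than fixing their spread gives a milder t-test departure: 4.3% at a between-hospital SD of 0.5 and 3.5% at 0.75. If hospitals differ only in VAS level, equally at baseline and week 8, the difference cancels in the change score and the error rate stays at about 5%.

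**The case against.** The strongest reply is that nothing here is invalid. A change-score comparison under randomization is unbiased, the trial is a feasibility pilot, and the article sets no power target that could be missed. All of that stands.

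A reader might go further than the article allows in four ways.
- **That the error rate is wrong.** This needs hospitals to differ in VAS change, and the article does not say whether they do. Even then the test rejects too seldom, so there is no added false-positive risk, and the effect is small at a hospital share of 0.05 or less.
- **That a change score is inefficient unless rho is near 1.** This is true only with equal SDs. The condition for full efficiency is a slope of 1, and the entry limit may bring the slope close to that.
- **That the baseline is ignored.** It is used, with a fixed slope.
- **That the pilot is underpowered.** The power figures above rest on assumed inputs and contradict nothing in the article.

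It can also be said that covariates are often left to a full protocol or SAP, which is not shown. That carries less weight, because the article does more than stay silent: it names the tests for the primary and secondary outcomes, and they are two-sample tests. A rule for choosing between t and Mann-Whitney may well stand elsewhere, and its absence is not the point made here.

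**Conclusion.** The point holds as a matter of efficiency. The stated primary test omits the stratification factor and fixes the baseline slope at 1, and so generally loses precision. For rho between 0.3 and 0.7 with equal SDs, ANCOVA would have 65% to 85% of the variance. With a baseline SD well below the week-8 SD, the gain may be close to zero. Which case applies cannot be told from the article.

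Conservatism is conditional on hospitals differing in VAS change. The article does not support reading the plan as anti-conservative, biased or invalid. The change is still worth making: apart from the degrees of freedom spent, ANCOVA is not less precise than the change score, so little is risked if the gain proves small.

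**What to change.** - Make the single primary analysis an ANCOVA of week-8 VAS with treatment, visit-2 VAS and hospital (three levels), or the equivalent week-8 contrast from a mixed model. Report the adjusted mean difference with its 95% CI.
- Name visit 2 as the baseline, since VAS is also taken at screening. Write the time point as week 8 (day 56, visit 4 in Table 1): the Efficacy section refers to V5, a label that Table 1 does not use.
- Use the same model for BT, CST and WHOQOL-BREF, each with its own baseline.
- Keep the unadjusted t or Mann-Whitney test as a sensitivity analysis.

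The cost is wording. Residual degrees of freedom fall from 60 − 2 = 58 to 60 − 5 = 55. No new data are needed, and SPSS, the software already named, can fit the model. Enrollment was still open when the article was published, with 50 of 60 recruited, so the change could have been fixed before unblinding.

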#### Primary outcome variable

##### Visual Analog Scale (VAS)

The mean changes of VAS score from baseline will be assessed the severity of CHHF symptoms by using a VAS [15, 16]. It is a 10-point scale ranging from 0 (no coldness) to 10 (most severe coldness). Patients will be asked to mark on the line at a point that represents the severity of the CHHF at every visit. The higher points represent greater severity of CHHF.

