### Statistical analysis

An independent statistics expert will perform the statistical analysis in a blind manner. Intention-to-treat (ITT) analysis will be the main analysis for efficacy assessment for use in all participants who receive at least one dose of any IP; in addition, per-protocol (PP) analysis will be performed in participants who complete the trial except dropouts. Missing data will be adjusted using the last-observation-carried-forward (LOCF) imputation method. The statistical level of significance will be set at *P* < 0.05. All statistical analyses will be performed using SPSS, version 25.0. (IBM Inc., Chicago, IL, USA).

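### The supplementary repeated-measures ANOVA uses raw post-baseline scores with no baseline term and mixes on-treatment visits with the off-treatment follow-up

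*Protocol article*

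**What the plan says.** After the main two-group comparisons, the Efficacy section of the protocol article states: "Additionally, the repeated measures analysis of variance (ANOVA) will be performed". Its response is "mean VAS, BT, and WHOQOL-BREF scores between groups at different time points (each visit after baseline assessment"). The response is therefore the score itself, at every visit after baseline.

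Table 1 lists three such visits: visit 3 (D28), visit 4 (D56) and FU1 (D84). On treatment length the text under Fig. 1 says "They will be administered the investigational products (IP) for 8 weeks", and on the last visit "one follow-up visit will be scheduled at 4 weeks after discontinuation of medication". FU1 is thus off treatment.

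Baseline values exist for all three measures, since Table 1 marks VAS, skin temperature and WHOQOL-BREF at visit 2. For VAS the outcome section adds: "Patients will be asked to mark on the line at a point that represents the severity of the CHHF at every visit".

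The primary endpoint does use baseline: "The primary endpoint is the mean change in VAS score between the OJS group and the placebo group from baseline to V5". Changes from baseline also define the secondary endpoints. Under Statistical analysis: "Missing data will be adjusted using the last-observation-carried-forward (LOCF) imputation method".

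For WHOQOL-BREF the outcome text says it "will be used and measured at visits 2 and 4", whereas Table 1 shows it at visits 2, 3, 4 and FU1.

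**The concern.** The sentence fixes two things, the response and the set of visits, and both choices are weak.

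First, the preceding sentence works with change from baseline and this one switches to scores, with no baseline value named in the model. With 30 per arm, chance imbalance at baseline and stable differences between patients then stay in the error term, although the data to remove them are collected anyway.

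Second, two on-treatment visits and one off-treatment visit are treated as one series. The Objective asks about symptoms after 8 weeks of medication, and the Abstract puts the primary outcome at week 8. An average over D28, D56 and D84 answers a different question, and one third of its weight falls after the drug has stopped. LOCF blurs this further: for a patient lost after D56 or D28, an on-treatment value is entered at FU1. No dropout rate is given, so that part cannot be sized.

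This is the only stated analysis that uses the repeated visits, in a pilot whose Discussion says its findings should inform a confirmatory trial.

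**Working it through.** **Inputs from the protocol.** 60 participants, 30 per group (Sample size calculation); significance at 0.05, taken as two-sided; post-baseline visits D28, D56 and D84 (Table 1). The protocol gives no effect size, SD, correlation or power, so there is no figure of its own to reproduce.

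**Assumptions.** Unit SD at each visit; equal correlation r between any two visits, at 0.3, 0.5 and 0.7; visit-4 effect 0.7 SD; no dropout.

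**Step 1, cost of leaving baseline out.**

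- Variance factor of a three-visit mean without baseline: (1 + 2r)/3.
- With the visit-2 value as covariate: (1 + 2r)/3 − r².
- Proportional cut: r² ÷ [(1 + 2r)/3].
- Single-visit contrast: the factor falls from 1 to 1 − r², a cut of r².

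| r | Three-visit mean, no baseline | With baseline | Cut | Cut, single visit |
|---|---|---|---|---|
| 0.3 | 0.533 | 0.443 | 17% | 9% |
| 0.5 | 0.667 | 0.417 | 38% | 25% |
| 0.7 | 0.800 | 0.310 | 61% | 49% |

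The standard error of the three-visit mean is multiplied by 0.91, 0.79 and 0.62. This gain does not depend on how the effect evolves over time.

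**Step 2, dilution if the group main effect is the term read.** The pooled effect is the mean of the three visit effects. With effects at D28/D56/D84 as multiples of the week-8 effect:

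- 1/1/1: (1 + 1 + 1)/3 = 100%
- 1/1/0.5: 2.5/3 = 83%
- 1/1/0: 2/3 = 67%
- 0.5/1/0: 1.5/3 = 50%
- 0.5/1/1: 2.5/3 = 83%. Here the shortfall comes from slow onset, not from FU1.

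**Step 3, power.** SE = √(2 × factor/30), noncentral t with 58 df (57 with the covariate).

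| Profile | Unadjusted three-visit mean, r = 0.3 / 0.5 / 0.7 | Baseline-adjusted visit-4 contrast |
|---|---|---|
| 1/1/1 | 95.5 / 90 / 85% | 80 / 87 / 96% |
| 1/1/0.5 | 86 / 78 / 70% | same |
| 1/1/0 | 68 / 59 / 51% | same |
| 0.5/1/0 | 45 / 37 / 32% | same |
| 0.5/1/1 | 86 / 78 / 70% | same |

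The visit-4 contrast depends only on the visit-4 effect, so its power is the same in every row. If the effect disappears by D84, it is well ahead of the pooled test. If the effect is fully sustained, it is behind at r = 0.3 and 0.5 and ahead at 0.7.

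**Step 4, WHOQOL-BREF.** The outcome text leaves one post-baseline value (visit 4), so there would be no repeated measure to analyse. Table 1 leaves three.

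**The case against.** A reader might infer that the plan pools the three visits and will therefore miss a real week-8 effect. The text does not support that. It does not say whether the group main effect, the group-by-time interaction or per-visit comparisons will be read, and its reference to differences at different time points fits the last two at least as well. Those average nothing. Dilution therefore needs both the main-effect reading and an effect that fades by D84.

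A reader might also infer that FU1 should simply be dropped. That can cost power. With slow onset and a sustained effect (0.5/1/1), an unadjusted mean of visits 3 and 4 has 70%, 64% and 58% power, against 86%, 78% and 70% with FU1 included. At r = 0.3 even the baseline-adjusted two-visit mean reaches only 76%, against 86% for the unadjusted three-visit mean.

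Nor is baseline ignored in the efficacy analysis as a whole. The primary and secondary endpoints are changes from baseline, the ANOVA is an addition, and the pilot has no power target. Nothing says that the ANOVA estimate in particular would feed the larger trial.

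Finally, model terms can be left to an analysis plan that is not shown. This stands in part: an unseen plan may name a covariate. But the article itself fixes the response and the visits, and that sentence needs amending either way.

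One limit on the baseline argument also stands. Under equal correlation, a pure group-by-time interaction among post-baseline visits gains nothing from the covariate, because baseline correlates equally with each visit and cancels in their differences. That interaction, however, has no power against a constant, sustained benefit, so it cannot replace a week-8 contrast.

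**Conclusion.** The point holds for the supplementary repeated-measures ANOVA and no further. As written, it compares raw scores without a baseline term and does not separate the off-treatment FU1 from D28 and D56.

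The firmest part is precision: a 17–61% cut in the variance of the three-visit mean, or 9–49% for one visit, is left unused for r between 0.3 and 0.7. It applies to the main effect and to per-visit contrasts under any effect profile.

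The dilution part is conditional. The pooled effect would be 50–83% of the week-8 effect in the fading profiles tried, and only if the main effect is read. With a persisting effect FU1 is harmless or helpful. All correlations, effect sizes and profiles are assumptions.

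**What to change.** Amend the sentence in the Efficacy section so that the repeated-measures model:

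- has the visit-2 value of the same outcome as covariate and a group-by-visit term;
- takes the visit-4 (D56) contrast as the on-treatment effect;
- reports the FU1 (D84) contrast separately, also baseline-adjusted, as persistence after stopping.

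Reconcile the WHOQOL-BREF outcome text with Table 1 before applying the model to that outcome. The Efficacy section's V5 does not appear in Table 1 and should be matched to a listed visit at the same time.

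The cost is about one sentence of analysis text and no new data. The downside is some power if the effect is fully sustained: 80% against 95.5% at r = 0.3 and 87% against 90% at r = 0.5, under the assumptions above. An all-visit, baseline-adjusted average could be shown beside it, labelled as covering both periods; under full persistence it has about 98% power or more.
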